**Methods:**

The nine-year follow-up study aims to reach all 1007 study participants (500 intervention and 507 control) from 60 randomized polling areas recruited to the original trial. Data are being collected in two phases. In phase 1 (Survey), we are admintsering a structured questionnaire, undertake physical measurements, and collect blood and urine samples for biochemical analysis. In phase II, we are inviting participants to undergo retinal imaging, body composition measurements, and ECG. All data collection is being conducted by trained Nurses. The primary outcome is the incidence of T2DM. Secondary outcomes include behavioral, psychosocial, clinical, biochemical, and retinal vasculature measures. Data analysis strategies include a comparison of outcome indicators with baseline, and follow-up measurements conducted at 12 and 24 months. Analysis of the long-term cost-effectiveness of the intervention is planned.

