Assessment of heart conditions		ECG	X	X	X	✓
Retinal microvasculature		Retinal imaging measures(Retinal architecture, arteriolar and venular diameters, and tortuosity) [44]	X	X	X	✓
Mortality		Status and self-reported causes of death	X	X	X	✓
Economic Evaluation	Healthcare utilization	Direct and indirect costs associated with outpatient and inpatient healthcare services, sources of financing, and time away from work due to ill health + SF-36	✓	✓	✓	✓
Community engagement	Sustainability	Sustainability – continued engagement in peer groups/activities; contacts with peer leaders; intention to continue engagement	X	X	X	✓

*WHO* World Health Organization, *SF-36*  Short Form 36, *MESA* Multi-Ethnic Study of Atherosclerosis, *OGTT*  Oral Glucose Tolerance Test, *TBC*  Total Blood Cholesterol, *HDL* High Density Lipoprotein, *LDL* Low Density Lipopotein

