### Economic evaluation

The economic evaluation involves cost-effectiveness analysis of the intervention from both the health system and societal perspectives. The key outcome measure will be Quality Adjusted Life Years (QALY), which will be estimated using the utility values (SF-6D) derived from the SF-36 survey form. Costs being assessed include both direct medical and non-medical costs and indirect (lost days of productivity) costs associated with the intervention. These are be based on information on staff inputs by duration and type and resource use collected during the study. Any additional “knock-on” effect on hospital admissions or outpatient service use is being quantified and costed for each study participant. We are calculating direct costs to the health service and patients from health facility records, project financial accounts, and participant responses to a survey including questions on health service use and spending. These analyses will be based on updated estimates for health facility costs and personal costs Personal costs to individuals will be collected as part of the questionnaire administered to study participants at nine years. These include transportation costs and out-of-pocket spending for health services use, especially for medications and will capture how the individual financed these costs (e.g., borrowing, asset sales, dis-savings). Any indirect costs to patients arising from being absent from work due to the intervention or illness are also being estimated. Savings from lowered health service use associated with the intervention are subtracted from intervention costs to derive incremental costs at the 9-year mark.

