### Statistical analysis

The two co-primary outcomes are diabetes incidence and CVD risk. The analyses will observe the intention-to-treat principle. A generalized estimating equation [46] model with appropriate link function and robust standard errors to account for clustering at polling areas will be fitted to estimate the relative risk (and 95% CI) for the co-primary outcomes at nine years. The sensitivity of the results to assumptions on the missing outcome data underlying this model will be examined using the method of multiple imputations to handle missing data and a pattern-mixture model.

To evaluate the treatment effect on continuous outcomes, a repeated measures mixed-effects linear regression model, adjusting for the baseline measures, will be fitted. Any skewed continuous outcome variable may be transformed before fitting this model. The model will specify treatment, time-point, and treatment by time-point interaction as fixed effects. Random effects will be specified for polling areas, to account for the clustered study design, and for participants, to account for correlation between the repeated measurements on the same participant. The estimated treatment effect (e.g., the absolute difference in means between the treatment arms) at nine years and two-sided 95% CI will be obtained. Binary other outcomes (e.g., diabetes) will be analyzed using GEE models similar to that of the co-primary outcomes.

The retinal image measurements will be compared between the treatment and control groups on the impact of a lifestyle modification program on pre-clinical changes in the retinal microvasculature and its correlation with cardiometabolic risk factors. Retinal imaging measures will include measures retinal architecture such as arteriolar and venular diameters and tortuosity.

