The economic evaluation will consist of a cost-effectiveness analysis that will compare the incremental costs and 9-year effects (QALYs) between the study groups. Generalized linear models (GLM) with gamma family and log link components will be used to estimate the incremental costs and QALYs and the results will be presented as incremental cost-effectiveness ratios (ICERs) [47]. QALY models will be adjusted for the baseline utility values (SF-6D). Uncertainty in the cost and QALY estimates will be estimated by non-parametric bootstrapping method [48] and the results will be graphically presented as cost-effectiveness planes and cost-effectiveness acceptability curves. Several sensitivity analyses will be carried out based on different assumptions about the costs, using different discount rates (3%, 5% and 10% per annum), and multiple imputation to assess the sensitivity of the main results due missing cost and QALY data.

Quantitative descriptive analyses will use key indicators—participation in group activities, maintenance of contact with peer leaders, interest to participate in group activities and recent effors made to improve lifestyle factors—to examine the extent of program sustainability from program participants perspectives. Statistical analyses will characterize the relationships among these indicators and the patterns of maintenance of other outcome measures over time.

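### The economic analysis names a baseline covariate for QALYs but none for costs, although healthcare costs were collected at baseline

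*Protocol article*

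**What the plan says.** The protocol article's Statistical analysis section treats both halves of the cost-effectiveness ratio together: "Generalized linear models (GLM) with gamma family and log link components will be used to estimate the incremental costs and QALYs". The covariate statement that follows concerns only one half: "QALY models will be adjusted for the baseline utility values (SF-6D"). The sensitivity analyses are then listed: "Several sensitivity analyses will be carried out based on different assumptions about the costs, using different discount rates (3%, 5% and 10% per annum"), together with multiple imputation for missing cost and QALY data. None of them adds baseline cost.

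The Economic evaluation section describes how net cost is built: "Savings from lowered health service use associated with the intervention are subtracted from intervention costs to derive incremental costs at the 9-year mark". It names no covariate either.

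Table 1 (Data collection instruments and measurements) has a single healthcare-utilisation row under economic evaluation: "Direct and indirect costs associated with outpatient and inpatient healthcare services, sources of financing, and time away from work due to ill health". It is ticked at baseline, 12 months, 24 months and nine years.

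For continuous outcomes in general, the Statistical analysis section does include a baseline term: "a repeated measures mixed-effects linear regression model, adjusting for the baseline measures, will be fitted".

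**The concern.** The economic paragraph goes down to covariate level and stops halfway. An analyst who follows the text would put an unadjusted cost difference over a baseline-adjusted QALY difference, with baseline cost data on file and unused.

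Cost-effectiveness is the third specific objective. There is only one realised allocation of 60 polling areas, and healthcare costs are usually skewed, so the arms may differ in baseline spending by chance. To the extent that a person's spending persists over time, part of that difference reappears in the follow-up cost difference, and so in the ratio, the cost-effectiveness plane and the acceptability curve. Conditioning on baseline cost removes that predictable part and lowers the residual variance. What is at stake is the precision and conditional accuracy of a secondary analysis. The co-primary outcomes are not affected.

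**Working it through.** **Is there a plan figure to reproduce?** The article states no sample size, power or precision for costs. The inputs borrowed here can be checked against the detectable effect stated under Sample size, Secondary outcomes: 0.23 SD with 415 control and 390 intervention participants, intra-cluster correlation 0.02, 80% power, two-sided 5%.

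- Formula: detectable effect = (1.96 + 0.84) × √[DE × (1/415 + 1/390)], with DE = 1 + (m − 1) × 0.02.
- m = 805/60 = 13.4: DE = 1.248, detectable effect 0.221 SD.
- m = 1007/60 = 16.8: DE = 1.316, detectable effect 0.227 SD.

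Both are close to 0.23, so the inputs are coherent.

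**Step 1. Size of a chance baseline imbalance.** The numbers are those expected at nine years; the abstract gives "all 1007 study participants (500 intervention and 507 control) from 60 randomized polling areas" as the randomised set. Applying the 0.02 correlation to costs is an assumption, since the article gives it for CVD risk and for continuous outcomes such as anthropometry and blood pressure.

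- SE = √[1.248 × (1/415 + 1/390)] = 0.079 SD.
- 95% of chance imbalances lie within ±1.96 × 0.0788 = ±0.154 SD.

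**Step 2. What adjustment would change.** Let rho be the correlation between baseline and follow-up cost. It is not in the documents, so a range is shown. Under linear analysis of covariance:

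- carry-over into the unadjusted cost difference = rho × baseline imbalance;
- proportional narrowing of the confidence interval = 1 − √(1 − rho²).

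| rho (assumed) | Variance removed (rho²) | Interval narrower by | Carry-over at the 0.154 SD limit |
|---|---|---|---|
| 0.1 | 1% | 0.5% | 0.015 SD |
| 0.2 | 4% | 2.0% | 0.031 SD |
| 0.3 | 9% | 4.6% | 0.046 SD |
| 0.4 | 16% | 8.3% | 0.062 SD |
| 0.5 | 25% | 13.4% | 0.077 SD |

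**Step 3. On the cost scale.** This needs a coefficient of variation, which is also not in the documents. Taking 1.5 to 2 as an assumption:

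- Imbalance at the 95% limit: rho 0.1 gives 0.0154 × 1.5 to 2 = 2.3% to 3.1% of mean cost; rho 0.3 gives 0.0463 × 1.5 to 2 = 7% to 9%; rho 0.5 gives 0.0772 × 1.5 to 2 = 12% to 15%.
- Median imbalance (0.6745 × 0.0788 = 0.053 SD) at rho 0.3: 0.053 × 0.3 × 1.5 to 2 = 2.4% to 3.2%.

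The larger percentages therefore need both an unlucky allocation and a fairly strong correlation.

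**Limit of the method.** These are linear results. The plan uses a gamma family with a log link, for which they are only an approximation.

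**The case against.** The strongest reply is that the article is silent about cost covariates; it does not say that costs will be left unadjusted. It condenses a fuller plan, and a covariate list for a secondary economic model is the kind of detail that may sit there. This stands in part: no decision against adjustment can be read from the text. It does not remove the point, because the paragraph does state covariates and gives them for one model only.

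Second, the asymmetry may have a reason. If QALYs are accumulated from utilities that include the baseline measurement, baseline utility is part of the QALY itself, whereas baseline cost is not part of cost after randomisation. That explains why utility was named first. It is not a reason to leave out baseline cost.

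Third, a reader might infer that the incremental cost is biased, or that every baseline difference in service use would be booked as a saving or a cost of the programme. The documents do not support either reading. Under randomisation the unadjusted difference is unbiased over repeated allocations, and chance imbalance is part of the variation that its interval reflects. Only rho times an imbalance carries over. The sentence on savings defines net cost; it does not fix an unadjusted estimator. Nor can the precision gain be turned into a power gain, since the article sets no power target for costs.

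Fourth, the baseline cost items may be imperfect as a covariate. Table 1 shows ticks but no recall periods or costing methods, and Economic evaluation refers to updated cost estimates at nine years. Raw skewed cost entered linearly under a log link could also have high leverage. Both points stand and shape the fix.

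**Conclusion.** The point holds as an inexpensive improvement to a secondary analysis. As written, the plan names a baseline covariate for QALYs and none for costs, although baseline healthcare costs were collected. The unadjusted incremental cost would be unbiased under randomisation, but it would carry the persistent part of any chance imbalance and forgo some precision.

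The size is uncertain. The interval would narrow by about 0.5% at rho 0.1, 2% at 0.2, 5% at 0.3 and 13% at 0.5. A low correlation between costs nine years apart cannot be excluded, so the gain may be small. These figures rest on an assumed rho and a linear approximation to a gamma, log-link model. The carry-over figures rest also on a borrowed intra-cluster correlation and, as percentages of mean cost, on an assumed coefficient of variation.

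**What to change.** In the economic paragraph of Statistical analysis, state that cost models will be adjusted for baseline healthcare costs and QALY models for baseline SF-6D utility. If the full plan already does this, saying so is enough. Also specify:

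- **Form of the covariate.** Prespecify one suited to a log link, for example log(cost + 1) plus an indicator for zero baseline cost.
- **Missing baseline cost.** Handle it under the multiple imputation already planned.
- **Reporting.** Give incremental cost as the model-standardised arm difference: predict each participant's cost under both arms, average, and subtract. A log-link coefficient is a ratio, whereas the cost-effectiveness ratio needs a difference.
- **Bootstrap.** Refit the adjusted model within each bootstrap sample.

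The cost is a few lines of text, minor extra modelling work and a check that the baseline cost items (recall period, costing method) are usable as a covariate. No new data are needed. Fixing the choice before costs are compared by arm also removes a later choice that could move the ratio.

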## Summary of Kerala Diabetes Prevention Program (K-DPP) findings at 12 and 24 months

The Kerala Diabetes Prevention Program (K-DPP) is a cluster randomized trial of a group-based and peer-led lifestyle intervention among adults at high-risk for type 2 diabetes in Kerala, India [5]. The intervention was adapted from evidence-based lifestyle interventions implemented in high-income countries, namely, Finland, the United States, and Australia [6]. A total of 60 polling areas (1007 participants) were randomized to the intervention arm (500 participants) or control arm (507 participants) in rural Kerala, India. The intervention was administered over 12 months period. Data on sociodemographic factors, lifestyle or behavioral factors, psychosocial, anthropometric, and biochemical measures were collected at baseline, 12 months, and 24 months. Among K-DPP participants, diabetes had developed in 17.1% of control participants and 14.9% of intervention participants (RR = 0.88; 95% CI: 0.66 -1.16, *P* = 0.36) at 24 months [7]. There was a significant reduction in diabetes incidence among a sub-group of participants with impaired glucose tolerance (IGT) (RR = 0.61, 95% CI: 0.41–0.92) in keeping with findings from the landmark clinical trials conducted on people with IGT [8–10]. The K-DPP program was also associated with a 32% reduction in 10-year cardiovascular disease (CVD) risk in the intervention group compared to the control group (RR = 0.68; 95% CI: 0.47–0.99; *P* = 0.047) among those aged 40 years or more [11]. Effectiveness evaluation has demonstrated significant improvements in certain key CVD risk factors and the physical functioning score of the health-related Quality of life (HRQoL) scale [7]. Moreover, this community-based peer-support lifestyle intervention was found to be cost-effective in individuals at high risk of developing diabetes in India over a 2-year period [11, 12]. The implementation evaluation has shown that the K-DPP program was feasible and acceptable in changing lifestyle behaviors in high-risk individuals [13]. Measures of program reach, adoption, and implementation were excellent for K-DPP. Twenty-nine of the 30 intervention communities delivered all intervention components. Two-thirds of intervention participants attended more than 50% of all peer-led group sessions and program recognition was high among local leaders and champions. There was also very strong community engagement and program sustainability in intervention communities at 24 months with 29/30 groups having conducted other diabetes prevention and health promotion activities in their communities [13].

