### Sample size

#### Primary outcomes

Based on the available data at 12 and 24 months, we anticipate more than 90% of K-DPP participants at baseline can provide complete and valid data for all key measures underlying diabetes incidence and 10-year CVD risk predicted using the Framingham Risk Score [28] at nine years. The proportion of participants (≥ 40 years of age at baseline) at high-rosk of CVD (with a predicted 10-year CVD risk greater than 20% [29]) is expected to be 34.5% in the control arm (*n* = 348) versus 17.9% in the K-DPP arm (*n* = 337) after nine years, assuming a linear increasing trend overtime based on our data so far. The power to detect this difference is more than 97% when accounting for an intra-cluster correlation of 0.02 at a two-sided 5% level of significance.

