#### Secondary outcomes

Loss to follow-up has been very low so far, i.e., < 5% at 24 months and a 7-year cohort study conducted in the same region had a follow-up rate of 92% [30]. Assuming missing data (i.e., no lost outcome data due to reasons such as loss-to-follow-up or no blood sample) reaches 18% in the control arm and 22% in the intervention arm, 415 and 390 participants in the control and intervention arm, respectively are predicted to provide data at 9-years of follow-up. With the sample sizes of 415 and 390 participants in the control and intervention arms respectively, we shall be able to detect an effect size (i.e., the absolute difference in means divided by standard deviation) in other continuous outcomes (e.g., anthropometric, BP, microvascular and cholesterol measurements) of 0.23 with 80% power at the two-sided 5% significance level, when accounting for an intra-cluster correlation of 0.02. Power was derived using power *twoprop* and *clustersampsi* in Stata software (version 17 StataCorp LP, College Station, TX, USA).

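### As written, the cost and QALY models and their bootstrap make no allowance for randomisation by polling area

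*Protocol article*

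**What the plan says.** In the protocol article, clustering is provided for in these places:

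- **Sample size, Primary outcomes:** for the CVD-risk comparison, "The power to detect this difference is more than 97% when accounting for an intra-cluster correlation of 0.02".
- **Sample size, Secondary outcomes:** "415 and 390 participants in the control and intervention arm, respectively are predicted to provide data at 9-years of follow-up", and the detectable standardised difference is given as one "of 0.23 with 80% power at the two-sided 5% significance level, when accounting for an intra-cluster correlation of 0.02".
- **Statistical analysis, co-primary and other binary outcomes:** GEE models with "robust standard errors to account for clustering at polling areas".
- **Statistical analysis, continuous outcomes:** a repeated-measures mixed model with random effects for polling areas and for participants.

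The economic paragraphs of the same section set up a separate analysis: "Generalized linear models (GLM) with gamma family and log link components will be used to estimate the incremental costs and QALYs". The QALY model is adjusted for baseline SF-6D. Then: "Uncertainty in the cost and QALY estimates will be estimated by non-parametric bootstrapping method". The results go into cost-effectiveness planes and acceptability curves. Sensitivity analyses vary the cost assumptions and discount rates and use multiple imputation. Polling areas are not mentioned in these paragraphs, and the unit that the bootstrap resamples is not stated.

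**The concern.** Participants in the same polling area were randomised together, and in the intervention arm they attended the same group sessions. If their costs or QALYs are positively correlated within area, an analysis that treats them as independent gives standard errors that are too small.

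The clustering provisions in the Statistical analysis section belong to the GEE and the mixed model. Costs and QALYs go through neither, so those provisions do not carry over. A programmer who followed the economic paragraphs literally would fit ordinary GLMs and resample participants.

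Cost-effectiveness is the third specific objective, and the article intends its findings to inform policy. The bootstrap is the stated source of uncertainty for the planes and acceptability curves, so an error in the resampling unit passes straight into them. Point estimates of the ICER need not change; what changes is how firmly they appear to be known.

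**Working it through.** **Inputs.** 60 polling areas and 1007 participants (Summary of K-DPP findings). 415 control and 390 intervention participants with nine-year data, and ICC 0.02 (Sample size, Secondary outcomes). The article gives no ICC for costs or QALYs. I borrow 0.02 and show 0 to 0.10 as an assumed range.

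**The article's own figure first.** Design effect DE = 1 + (m − 1) × ICC, and detectable difference = (1.960 + 0.842) × √(1/415 + 1/390) × √DE.

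- No clustering: 2.802 × 0.0705 = 0.198.
- m = 1007/60 = 16.8: DE = 1.316, giving 0.198 × 1.147 = 0.227 (0.231 using t on 58 df).
- m = 805/60 = 13.4: DE = 1.248, giving 0.198 × 1.117 = 0.221 (0.225 using t).

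The stated 0.23 is reproduced with clustering allowed for, and not without it.

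**Effect of leaving clustering out of the economic analysis.** The ratio of the participant-level SE to the correct SE is 1/√DE. Coverage of a nominal 95% interval is 2Φ(1.96/√DE) − 1. With m = 13.4:

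| ICC | DE | SE too small by | Coverage |
|---|---|---|---|
| 0 | 1.000 | 0% | 95.0% |
| 0.01 (assumed) | 1.124 | 5.7% | 93.5% |
| 0.02 (article) | 1.248 | 10.5% | 92.1% |
| 0.05 (assumed) | 1.621 | 21.5% | 87.6% |
| 0.10 (assumed) | 2.242 | 33.2% | 80.9% |

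With m = 16.8 and ICC 0.02, the SE is 12.8% too small and coverage is 91.3%.

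**Acceptability curve.** On a normal approximation, a participant-level probability of 0.95 should read Φ(1.645/1.117) = 0.93 at ICC 0.02. By symmetry, 0.05 should read 0.07. The error pushes probabilities away from 0.5 on both sides.

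**Simulation check.** 2000 simulated trials with a normal outcome, no effect, 30 areas per arm and 13 or 14 participants per area, using percentile bootstraps:

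| ICC | Participants resampled | Whole areas resampled |
|---|---|---|
| 0 | 95.3% | 93.9% |
| 0.02 | 91.6% | 93.8% |
| 0.05 | 86.7% | 92.9% |
| 0.10 | 80.8% | 94.1% |

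The participant-level column agrees with the formula. Resampling whole areas restores most of the lost coverage. It stays a point or two under 95%, which is expected with only 30 units per arm.

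**Which cluster bootstrap.** Resampling areas and then participants within them, without correction, counts the within-area variance about twice. Take ICC 0.02, m = 13, k = 30 areas per arm and total variance 1.

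- True variance of an arm mean, times k: 0.02 + 0.98/13 = 0.0954.
- Two-stage bootstrap variance, times k: (29/30) × 0.0954 + (12/13) × 0.0754 = 0.0922 + 0.0696 = 0.1618.
- SE ratio: √(0.1618/0.0954) = 1.30.

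A simulation of 600 trials gave 1.29 with coverage of 98.7%, against 0.97 to 0.98 for the SE when only whole areas are resampled. The uncorrected two-stage version would overshoot by more than the problem it is meant to cure.

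**The case against.** The strongest reply is that this rests on silence. Resampling whole polling areas is also a non-parametric bootstrap, a GLM can carry cluster-robust standard errors, and a condensed article may leave both to a fuller plan. That stands as far as it goes: a reader might infer that the investigators have decided to ignore clustering, and the text does not support that. However, the economic paragraphs are not sparse. They give the distribution family, link, covariate, uncertainty method, graphical outputs, discount rates and imputation, and the same section spells out clustering for the main models shortly before. What is specified, if run as written, is a single-level analysis.

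Several stronger readings should be resisted:

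- **That every effectiveness model handles clustering and only the economic one does not.** The retinal comparison names no clustering method either.
- **That costs cluster more strongly than clinical outcomes.** This may be so, but the article gives no such figure. The 0.05 and 0.10 rows are assumptions.
- **That the probability of cost-effectiveness would be overstated.** That is true only where estimated net benefit is positive. Where it is negative, the probability would be understated.
- **That a gamma family is an error for QALYs, or fails on zero costs.** The article gives no QALY distribution and no sign of zero totals, and uncertainty comes from the bootstrap rather than the gamma likelihood. This is largely a modelling preference.

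**Conclusion.** The point holds in a limited form. As specified, the economic analysis makes no allowance for the unit of randomisation, whereas the power statements and the main binary and continuous outcome models do. If participants are resampled individually, the effect at ICC 0.02 is moderate: standard errors 10% to 13% too small and coverage of 91% to 92%, depending on whether 13.4 or 16.8 participants per area is used. It grows to coverage of about 88% to 81% under assumed ICCs of 0.05 to 0.10 (13.4 per area), and vanishes if the ICC is zero.

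The figures assume areas of equal size, all 60 areas still contributing, and a normal approximation. The two co-primary analyses are not affected. This is worth correcting because it bears on a specific objective and costs little; it does not threaten the trial's main conclusions.

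**What to change.** Add to the economic part of the Statistical analysis section:

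- The bootstrap resamples whole polling areas, separately within each arm. Each participant's cost and QALY stay paired, and both models are refitted in every replicate. There is no second-stage resampling of participants unless a shrinkage correction is applied.
- Any model-based standard errors from the cost and QALY GLMs are clustered by polling area.
- The multiple imputation of cost and QALY data respects the clustering.

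If a fuller analysis plan already says this, a brief statement in the article is enough. The cost is a short addition to the text and a few lines of code, while follow-up is still in progress. The price is somewhat wider intervals and flatter acceptability curves: at ICC 0.02, standard errors about 12% larger than the participant-level ones (√1.248 = 1.117).

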### Data collection instruments and measurements

Most of the measurements undertaken in previous rounds of assessment are also undertaken in this follow-up assessment (Table 1). A detailed description of these measurements has been published [5]. Newly added measurements include an assessment of the retinal microvasculature, ECG, multimorbidity questionnaire, urine albumin, serum creatinine, sedentary behavior, and community engagement/sustainability questions. The measurements used in all rounds of assessment are summarized in Table 1 below.

**Table 1 Tab1:** Measurements included in the four time points of assessment

Variable	Component	Measurement tools/questions	Baseline	12 months	24 months	9-Years
Socio-demography	Age, sex, marital status, education, religion, occupation, household size, and monthly household expenditure		✓	✓	✓	✓
Behavioral measures	Tobacco use	WHO STEPS questionnaire [32]	✓	✓	✓	✓
	Alcohol use	WHO STEPS questionnaire [32]	✓	✓	✓	✓
	Physical activity	Global Physical Activity Questionnaire [33]	✓	✓	✓	✓
	Sedentary behavior	Sitting and screen time	X	X	X	✓
	Sedentary behavior	Time spent in front of a screen [34]	✓	✓	✓	✓
	Diet	Food Frequency Questionnaire [35]	✓	✓	✓	X
Diabetes knowledge	Barriers to healthy eating	Scale designed for trial	✓	✓	✓	✓
	Barriers to PA	Adapted from Booth et al. [36]	✓	✓	✓	✓
	Self-efficacy	Adapted Schwarzer and Renner [37]	✓	✓	✓	✓
Psychosocial measures	Depression	Patient Health Questionnaire-9 [38]	✓	✓	✓	✓
	Stress	Chronic stress scale used in MESA study [39]	✓	✓	✓	✓
	Anxiety	General anxiety disorder scale [40]	✓	✓	✓	✓
	HRQoL	Short Form-36 [41]	✓	✓	✓	✓
	Social support	ENRICHD social support scale [42]	✓	✓	✓	✓
	Life satisfaction	Single question: Satisfaction with life	✓	✓	✓	✓
Medical history	Medical history	CVD and diabetes-related medications	✓	✓	✓	✓
	Family history	Updated family history of disease	✓	✓	✓	✓
	Multimorbidity	Adapted from the WHO SAGE questionnaire [43]	X	X	X	✓
Clinical measures	Anthropometry	Waist circumference (Seca measuring tape)	✓	✓	✓	✓
		Height (Seca stadiometer)	✓	✓	✓	X
		Weight and body composition (TANITA)	✓	✓	✓	✓
		Bioimpedance (TANITA)	✓	✓	✓	✓
	Blood pressure	Omron automatic blood pressure monitor	✓	✓	✓	✓
Biochemical measures	Pathology	Glycaemic control (fasting plasma glucose)	✓	✓	✓	✓
		Glycaemic control -OGTT	✓	✓	✓	X
		Glycaemic control (HbA1c)	✓	✓	✓	✓
		Lipid profile (TBC, HDL, LDL, triglycerides)	✓	✓	✓	✓
		Serum creatinine	X	X	X	✓
		Urine albumin	X	X	X	✓

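### The headline cost-effectiveness result is by implication complete-case, with multiple imputation kept as a sensitivity check; the two roles are better swapped.

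*Protocol article*

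**What the plan says.** All references are to the protocol article.

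- **Main economic model** (Statistical analysis): "Generalized linear models (GLM) with gamma family and log link components will be used to estimate the incremental costs and QALYs". The comparison will "compare the incremental costs and 9-year effects (QALYs) between the study groups".
- **Covariates** (same section): the only one named for QALYs is baseline SF-6D utility. None is named for costs.
- **Missing data** (same section): imputation appears only in the list of sensitivity analyses, as "multiple imputation to assess the sensitivity of the main results due missing cost and QALY data". No missing-data method is named for the main result.
- **Source of QALYs** (Economic evaluation): utilities, "which will be estimated using the utility values (SF-6D) derived from the SF-36 survey form". Table 1 ticks the SF-36 at baseline, 12 months, 24 months and nine years.
- **Costs**: Table 1 ticks healthcare utilisation at the same four rounds, with none between 24 months and nine years. The Economic evaluation section adds: "Personal costs to individuals will be collected as part of the questionnaire administered to study participants at nine years".
- **Expected missingness** (Sample size, Secondary outcomes): it "reaches 18% in the control arm and 22% in the intervention arm", leaving 415 and 390 participants. The Primary outcomes paragraph instead anticipates over 90% with complete data on the key diabetes and CVD measures.

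**The concern.** A nine-year QALY or cost is a total over several rounds. A GLM fitted to one total per person omits anyone whose total cannot be formed. If imputation serves only to check the main result, a participant missed at year nine leaves the headline analysis, and their three earlier rounds go with them.

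The same article treats its other continuous outcomes differently. They go into a repeated-measures mixed model, which keeps a participant's observed rounds when another round is missing. The SF-36 answers of one person could thus be kept in one analysis and dropped in the other.

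Two things are at stake. The first is bias: the main QALY model conditions on arm and baseline utility only, so dropout that also depends on health at 12 or 24 months, or on earlier spending, is not handled. The second is precision: observed information is set aside in the ICER and acceptability curve that will be quoted.

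**Working it through.** **1. The plan's own counts.** 507 × 0.82 = 415.7 (stated 415) and 500 × 0.78 = 390 (stated 390). Missing: 507 − 415 = 92 and 500 − 390 = 110, so 202 of 1007 = 20.1%. Under the Primary outcomes retention figure, fewer than about 100 would be missing (10% of 1007). Loss at 24 months is reported as under 5%, so most of those missed at year nine should have their earlier rounds.

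**2. QALY weight on the observed rounds.** Assumption, not in the article: straight-line interpolation between rounds at 0, 1, 2 and 9 years. Undiscounted trapezoid weights:

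- baseline: (1 − 0)/2 = 0.5
- 12 months: (2 − 0)/2 = 1.0
- 24 months: (9 − 1)/2 = 4.0
- nine years: (9 − 2)/2 = 3.5

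The sum is 9. For someone missing only year nine, observed utilities carry 5.5/9 = 61% of the weight (64%, 65% and 69% at discount rates of 3%, 5% and 10%). By calendar time, only 2/9 = 22% lies between observed visits.

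**3. Precision of the QALY contrast, ignoring clustering.** Assumptions: equal SDs (set to 1), a common between-round correlation ρ of 0.2 to 0.6, and ideal imputation from the three earlier rounds.

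- Variance of the QALY: 29.5 + 51.5ρ, where 29.5 is the sum of squared weights and 51.5 = 81 − 29.5.
- Covariance with baseline utility: 0.5 + 8.5ρ.
- Variance after baseline adjustment, V = 29.5 + 51.5ρ − (0.5 + 8.5ρ)².
- Part not predictable without year nine, U = 3.5² × [1 − 3ρ²/(1 + 2ρ)].
- R² beyond baseline = 1 − U/V.
- Variance relative to full data, with f = 805/1007 = 0.799: complete-case 1/f = 1.251; imputed 1 + (1 − R²)(1/f − 1).

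| | ρ = 0.2 | ρ = 0.6 |
|---|---|---|
| V | 39.80 − 2.2² = 34.96 | 60.40 − 5.6² = 29.04 |
| U | 12.25 × 0.914 = 11.20 | 12.25 × 0.509 = 6.24 |
| R² beyond baseline | 0.680 | 0.785 |
| Imputed variance | 1.080 | 1.054 |
| SE ratio, complete-case to imputed | √(1.251/1.080) = 1.076 | √(1.251/1.054) = 1.089 |

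At 10% missing (f = 0.9), the complete-case variance is 1.111 and the imputed variance 1.036 to 1.024, so the SE ratio is 1.036 to 1.042.

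**4. With clustering.** Use the ICC of 0.02 from the sample-size section and 60 polling areas, and take the variance as proportional to 0.02/60 + (0.98/1007) × (the factor from step 3). Applying that ICC to the adjusted QALY is an assumption.

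- Complete-case, 20% missing: 0.000333 + 0.000973 × 1.251 = 0.001551.
- Imputed: 0.001385 (ρ = 0.2) to 0.001359 (ρ = 0.6). The SE ratio is 1.058 to 1.068.
- Ceiling, with every missing person fully recovered: √(0.001551/0.001306) = 1.09.

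**5. Costs.** No parallel figure can be given. There is no cost round between 24 months and nine years, so for a person missed at year nine most of the cost period is unobserved and earlier rounds recover less.

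**The case against.** The strongest case on the other side is that multiple imputation is already prespecified, so both estimates will be reported and the change only exchanges labels. The co-primary analyses follow the same pattern, with imputation and a pattern-mixture model as sensitivity analyses. The article is also a condensed account, and how totals are formed may be set out in a fuller document. This stands in part. It limits the size of the point, but it does not remove it: the article itself gives imputation the secondary role, and the base-case label decides which ICER is quoted.

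A reader might infer more than the documents support:

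- *That a complete-case analysis is stated.* It is not. It follows from imputation being set against the main results and from a GLM on per-person totals.
- *That 20% will be lost.* This is a planning assumption for the power of other continuous outcomes, and the article elsewhere expects under 10%. Mortality status is collected, so known deaths need not count as missing.
- *That most of these people's nine years are already observed.* This is true only as 61% of interpolation weight. By time it is 2 of 9 years, and it does not carry over to costs.
- *That the main QALY result needs dropout to be unrelated to all earlier health.* Dropout depending only on arm and baseline utility would not bias a correctly specified model, because "QALY models will be adjusted for the baseline utility values (SF-6D").
- *That 18% against 22% shows bias.* A difference in dropout rates alone does not, and no direction or size of bias in the ICER can be derived from the article.

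**Conclusion.** The point holds as a modest, inexpensive improvement. The headline economic analysis is by implication complete-case. It would omit up to about 20% of participants under one of the article's retention assumptions and under 10% under the other, leaving their earlier utility and cost rounds unused.

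The main reason to change is possible bias from dropout related to 12- or 24-month health or to earlier spending, whose size cannot be given from the article. The precision loss is secondary. For QALYs at 20% missing it is about 8% to 9% on the standard error without clustering and about 6% to 7% with an ICC of 0.02. At 10% missing it is about 4% without clustering. These figures rest on linear interpolation, equal SDs, exchangeable correlations of 0.2 to 0.6, attendance at all earlier rounds and ideal imputation; real imputation would gain somewhat less. The gain for costs is smaller and is not quantified.

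**What to change.** In the economic paragraph of Statistical analysis, exchange the two roles:

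- **Base case:** the multiply imputed analysis. Impute at round level rather than on the nine-year total, separately by arm, with polling area in the imputation model and the earlier SF-6D and cost rounds as predictors. Treat known deaths as observed, not as values to impute.
- **Sensitivity analysis:** the complete-case ICER, with the number analysed in each arm.

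The cost is a change of wording. The imputation is already planned, no new data are needed, and the article reports follow-up as still under way. The small downside is that the base case then depends on the imputation model; the retained complete-case result serves as the check on it.
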